**Methods:**

This study evaluates the efficacy of the intervention Understanding Your Baby (UYB) compared to Care As Usual (CAU) in 10 Danish municipalities. UYB aims at promoting parental competence in new parents by supporting them in noticing their infants’ behavioral cues and interpreting them in terms of mental states. Participants will be approximately 1,130 singletons and their parents. Inclusion criteria are first-time parents, minimum 18 years old, living in one of the 10 municipalities, and registered in the Danish Civil Registration Register (CPR). Around 230 health visitors deliver the UYB as part of their routine observation of infant social withdrawal in the Danish home visiting program. During an interaction between the health visitor and the infant, the health visitor articulates specific infant behaviors and helps the caregivers interpret these behaviors to mental states. The study is a controlled parallel group study with data obtained at four time points in two phases: First in the control group receiving the publicly available postnatal care (CAU), secondly in the intervention group after UYB implementation into the existing postnatal services. The primary outcome is maternal competence. Secondary measures include paternal competence, parental stress, parental mentalizing, and infant socioemotional development. Analysis will employ survey data and data from the health visitors’ register.

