### Purpose of the study

The purpose of the current study is to evaluate the efficacy of the newly developed UYB program in 10 Danish municipalities. More specifically, the aim of the study is to test whether Care As Usual (CAU) including the UYB program in comparison to CAU alone will lead to:Improved maternal competence (primary outcome)Improved paternal competence (secondary outcome)Improved parental mentalizing, i.e. reflective functioning and mind-mindedness (secondary outcome)Reduced parental stress (secondary outcome)Improved infant socioemotional development (secondary outcome)Reduced infant social withdrawal (secondary outcome)Reduced parental media use and infant screen time (secondary outcome)Increased information about infant socioemotional development (secondary outcome)Heterogeneity of effects across family types with more disadvantaged families and families met with more intensive UYB implementation gaining more from participation in the intervention (tertiary outcome)

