### Participants

#### Inclusion criteria

Parents living in one of the 10 municipalities participating in the project are invited to participate in the study. The parents have to be registered in the Danish Civil Registration Register (CPR) as parents to a newborn baby to be invited for the study. Mothers are invited if they are first-time mothers and if they are living on the same address as the child. Fathers/partners are invited if they have custody of the child or if they are living on the same address as the child, and they are invited regardless of whether they have children from previous relationships or not.

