### The Understanding Your Baby intervention

In the study’s second phase, the experimental group of first time parents receives the UYB integrated into the existing publicly available postnatal care services, i.e. the amount of potential delivered UYB range from one to five in the 10 municipalities (see Table 2). The UYB is delivered by health visitors to all first-time parents during routine home visits.

The UYB is a universal educational parenting intervention aimed at supporting and promoting parents’ curiosity and knowledge about their infants’ socioemotional needs, ability to meet their infants’ needs, and thereby facilitating the development of a secure attachment and infant optimal socioemotional development. The UYB uses the routine ADBB observational situation as a standardized setting for a systematic sharing of knowledge and a dialogue with parents about their infants’ socioemotional cues, needs, and development in all families—i.e. this dialogue takes place in all cases—whether or not the ADBB observation gives rise to a concern regarding the infant’s socioemotional development. Although the primary purpose of the ADBB observation is early identification of persistent infant social withdrawal, the ADBB also provides an optimal context to guide caregivers about their child’s social and emotional development. During the interaction between the health visitor and the infant, the health visitor articulates specific infant behaviors and help the caregivers to interpret these behaviors in terms of mental states. For instance, when the infant looks away, the health visitor may explain to the parents that the infant needs a break to regulate themselves because interaction and eye contact is very stimulating for small children. In this way, the parents are shown their infant’s behavioral cues and how these behaviors are expressions of the inner world of the infant.

The UYB consists of four elements, each of which are described in the following: The UYB manual, the UYB dialogue cards, the UYB online video library, and UYB profiles on the social media platforms Facebook and Instagram.

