The UYB manual entails an overview of research-based knowledge about infants’ socioemotional development and needs across four age groups (0–2, 2–4, 4–8, and 8–12 months) and five central behavioral areas inspired by the following items from the ADBB: Facial expressions (item 1), Eye contact (item 2), General level of activity (item 3), Vocalizations (item 5), Relationship and Attraction (items 7 and 8). In addition, the manual contains three chapters on significant themes for infant socioemotional development: infant crying, ‘good enough’ parenting, and screen time in the family. The manual provides the health visitors with the newest research-based knowledge on infant socioemotional development and enables them to provide research-based information to parents during the ADBB observations and when using the dialogue cards.

The UYB dialogue cards consist of four laminated cards, one that is mandatory and three that are optional for the health visitors to use. The mandatory UYB dialogue card is developed to support sharing of knowledge and facilitate reflection about the infant’s socioemotional cues and needs. The card displays the five areas from the ADBB also described in the manual. On the front of the card, short questions describe what the health visitor is observing when examining each of these areas, e.g. “What emotions does the baby express with his/her face?” (Facial Expressions). On the back of the card, short sentences describe how parents can support their infant’s development in relation to each of the areas, e.g. “Eye contact gives the baby a feeling of closeness and security. Breaks give the baby an opportunity to self-regulate. Notice when your baby seeks eye contact and when your baby needs a break.” This dialogue card should be used every time the health visitors conduct ADBB screenings in first-time families to inform parents about the specific areas related to infant social contact. Health visitors are also encouraged to use the card to provide feedback to parents about their infant’s behavior on each of these areas and guide parents in relation to how to support their child’s socioemotional development, also using age-specific and research-based knowledge from the manual.

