### Background information and control variables

*Background information* about the parents is obtained as part of the 2- and 11-months questionnaire. At 2 months, this information includes questions about parental age, gender, ethnicity, educational background, employment status, income, relationship status, smoking, persons living in the household, the birth weight of the child, birth complications, and siblings to the child. At 11 months, parents are asked about breastfeeding, parental leave, and parental involvement with the child.

*Parental depressive symptoms* will be measured using the Edinburgh Postnatal Depression Scale (EPDS; [44]) or the Gotland Male Depression Scale (GMDS; [45]). The EPDS is a screening instrument for postnatal depression, which has primarily been validated in female samples. The EPDS contains 10 items assessing the presence of depressive symptoms in the past seven days (e.g. “I have felt sad and miserable”). Each item is rated on a four-point scale from “No, not at all” (= 0) to “Yes, quite a lot” (= 3). GMDS is a screening tool for male depression and consists of 13 items assessing whether the respondent’s behavior has changed during the last month (e.g. “More aggressive, outward-reacting, difficulties keeping self-control”). Each item is rated on a 4-point Likert type scale from “Not at all” (= 0) to “Extremely so” (= 4) [46]. For both questionnaires, items are summed to a total score with higher scores reflecting higher levels of depressive symptoms. These questionnaires are routinely given to parents typically around 8 weeks postpartum as part of the health visitors’ mental health screening program. The parents fill in the questionnaires during the health visitor’s visit in either a web-based or paper-and-pencil manner. The EPDS and GMDS data will be obtained from the health visitors’ register.

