### Statistical methods

The analyses of both primary and secondary outcomes will be conducted under the intention to treat principle where the participants are analysed according to their control CAU/intervention UYB status. However, as a secondary analysis, we will also conduct analyses where the actual intervention participation is taken into account (i.e. whether the families in the UYB group have been given the intervention by the health visitors). Thus, we will perform a contamination adjusted intention to treat analysis [61] which compliments the intention-to-treat approach by producing a better estimate of the effect of the UYB intervention.

The primary endpoint is PSOC at 11 months postpartum. The level of significance will be 5%, two-tailed [62]. The primary comparison of UYB and CAU interventions is analysed using linear mixed models with the health visitor as the second order variable. This is done to account for the correlation induced by the same health visitor conducting the CAU and UYB intervention for multiple families. We will control for maternal educational level in years, maternal level of depressive symptoms, and maternal age in years.

Secondary outcomes will be analysed in the same way as the primary outcome. Binary and categorical outcomes will be analysed with mixed logistic and multinomial logistic regressions, respectively, and continuous outcomes with mixed linear regression analyses. For outcomes where we are interested in the individual variance across time points, generalized estimating equations will be employed. All the analyses will be adjusted for the abovementioned covariates. As multiple tests will be conducted, we will both assess significance using the 5% significance level and adjust for multiple testing using the Bonferroni-Holm method [63].

For the tertiary outcome, we investigate whether some subpopulations benefit more from the UYB intervention. These subpopulations will be defined as disadvantaged families (e.g. based on background information such as employment status, income, etc.) versus advantageous families as well as families with a more intensive UYB implementation. In practice, we will test for significant subpopulations-group status interaction effects using linear moderation analyses (as otherwise described above).

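### The groups are described as first-time parents, but fathers and partners are enrolled whatever their earlier children, and the paternal models do not adjust for this.

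*Protocol article*

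**What the plan says.** **Population as described.** The Methods paragraph of the abstract states: "Inclusion criteria are first-time parents, minimum 18 years old, living in one of the 10 municipalities". The sections Care As Usual and The Understanding Your Baby intervention use the same description for the control and intervention groups. On delivery, the latter says: "The UYB is delivered by health visitors to all first-time parents during routine home visits".

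**Population as enrolled.** Under Inclusion criteria the limit is on mothers: "Mothers are invited if they are first-time mothers and if they are living on the same address as the child". Fathers and partners qualify by custody or shared address, and "they are invited regardless of whether they have children from previous relationships or not".

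**Outcome and analysis.** Purpose of the study lists paternal competence first among the secondary outcomes; it is measured with the PSOC. Statistical methods names three covariates for the primary analysis: maternal education in years, maternal depressive symptoms and maternal age. Secondary outcomes follow the same approach, and "All the analyses will be adjusted for the abovementioned covariates". The tertiary subgroups concern family disadvantage and intensity of implementation, not whether the father already has children.

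**Data at hand.** The 2-month background questions include "persons living in the household, the birth weight of the child, birth complications, and siblings to the child". No use of the sibling item in the analysis is stated.

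**The concern.** For mothers, eligibility removes earlier parenting experience as a possible confounder. For fathers and partners, neither eligibility nor the model does so.

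This matters more here than it would in a randomised trial. Under Study design, the care-as-usual group is recruited first and the intervention group only after the health visitors have been trained. Under Dates defining periods of recruitment and follow-up, the control births run from April to September 2019. The intervention births run from January to June 2021 in seven municipalities and from April to September 2021 in three. Nothing in that scheme keeps the share of experienced fathers equal.

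The PSOC measures felt competence. The Background section rests on the idea that the transition to parenthood demands new skills, so a father who has been through it before may plausibly score differently. That is an inference from the protocol's rationale, not a figure that it gives.

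Two things are at stake: a possible bias in the paternal comparison, and the population to which the paternal result may be said to apply.

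**Working it through.** **1. The passages side by side**

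| Place in the protocol article | Mothers | Fathers/partners |
|---|---|---|
| Abstract, Methods | first-time | first-time (as 'parents') |
| Care As Usual; The Understanding Your Baby intervention | first-time | first-time (as 'parents') |
| Inclusion criteria | first-time | earlier children allowed |
| Statistical methods, covariates | education, depressive symptoms, age | none of their own |

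The descriptions of the groups and the enrolment rule differ for fathers. The covariate set does not close the gap. Even if a reader took it that the father's own education, depressive symptoms and age would replace the mother's in his models, which the text does not say, earlier children would still not be among them.

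**2. Size of the possible bias**

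The protocol gives no figure on this point to reproduce. The only figure taken from it is the design effect d = 0.2 (Sample size). The rest is assumed:
- difference between phases in the share of fathers with earlier children, Δp: 0.01 to 0.05
- standardised PSOC gap between experienced and first-time fathers, g: 0.2 to 0.5 SD
- the maternal covariates pick up none of this difference

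Bias = Δp × g, and relative bias = Δp × g / 0.2.

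| Δp | g = 0.2 | g = 0.3 | g = 0.5 |
|---|---|---|---|
| 0.01 | 0.002 (1.0%) | 0.003 (1.5%) | 0.005 (2.5%) |
| 0.02 | 0.004 (2.0%) | 0.006 (3.0%) | 0.010 (5.0%) |
| 0.05 | 0.010 (5.0%) | 0.015 (7.5%) | 0.025 (12.5%) |

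The sign is unknown: it depends on which phase has more experienced fathers and on whether they score higher or lower.

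**3. Effect on precision**

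The number of fathers is not stated, so take 345 per group (690 / 2) as an assumption. The plain two-sided formula for d = 0.2, 80% power and 5% significance gives 393 per group, 786 in all. The planned 690 corresponds to a residual variance of 690 / 786 = 0.878, which would mean that the covariates explain about 12% of the variance. The protocol does not state that value; it is used here only to start from 80% power.

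A mixture with share p and gap g adds variance p(1 − p)g². At the least favourable assumed values this is 0.20 × 0.80 × 0.5² = 0.04. The residual SD becomes √(0.878 × 1.04) = 0.956, the standard error 0.956 × √(2/345) = 0.0728, and the power Φ(0.2/0.0728 − 1.96) ≈ 0.785. The loss is therefore at most about 1.5 percentage points within these assumptions.

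**The case against.** The strongest reply is that the father rule is deliberate, openly stated, and the same in both phases and all 10 municipalities. The programme is delivered in the home, so inviting the partner of every first-time mother fits who receives it. The abstract merely shortens this. That stands as a defence of the rule: enrolling these fathers is not a design fault. It does not cover the descriptions of the groups in the body of the article, or the covariate set.

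A second reply is that singling out earlier fatherhood is a preference, since the father's own age, education and depressive symptoms are also absent from the covariates. In part this stands. Earlier fatherhood still differs from those, because it is the one characteristic on which the protocol says that the groups are uniform when the fathers are not.

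A third is that the sibling item may not count the father's children who live elsewhere. This also stands in part. Because enrolled mothers are first-time mothers, a reported sibling should come through the father or partner, so the item is informative, but under-reporting is possible.

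Two stronger readings are tempting and are not supported:
- **That fathers of a couple's second child are eligible.** The sentence on fathers does not repeat the condition on the mother. But it waives only children from previous relationships, which would be pointless if later children of the same couple qualified. The delivery text points the same way: "This dialogue card should be used every time the health visitors conduct ADBB screenings in first-time families".
- **That dilution biases the result.** If 5% to 20% of fathers were experienced and gained nothing, an effect of 0.20 would become 0.20 × 0.95 = 0.19 to 0.20 × 0.80 = 0.16. For fathers as enrolled, that smaller value is the intention-to-treat effect. It would be wrong only if reported as the effect in first-time fathers, and the stated aim speaks of paternal competence without that limit.

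**Conclusion.** The point holds in a limited form. The article describes both groups as first-time parents while enrolling fathers and partners regardless of earlier children. It then fixes a covariate set that leaves any difference between phases in this respect unadjusted. The pooled paternal result cannot be presented as an effect in first-time fathers.

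The likely numerical effect is small: 0.002 to 0.025 SD, or 1% to 12.5% of the design effect, with little loss of power. Every input apart from the design effect is assumed, and nothing in the documents shows that the share of experienced fathers did change between 2019 and 2021. The outcomes concerned are the secondary ones that fathers report. The primary endpoint, maternal PSOC at 11 months, is untouched because mothers are first-time mothers by rule. The change is worth making because it costs little, not because the bias is expected to be large.

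**What to change.** 1. In the abstract and in the sections Care As Usual and The Understanding Your Baby intervention, state that 'first-time' refers to the mother and that fathers and partners may have earlier children.
2. Add a yes/no term for the father's or partner's own earlier children to all father-reported outcome models. Use the sibling item from the 2-month questionnaire, after checking whether it captures children living elsewhere.
3. Pre-state a sensitivity analysis of paternal PSOC restricted to first-time fathers, and report the share of experienced fathers in each phase.

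The cost is some wording and one extra covariate, with no change to recruitment or visits. The downsides are possible misclassification if non-resident children were not reported, and fewer fathers in the sensitivity analysis.

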#### Exclusion criteria

Parents younger than 18 years, parents who are legally incapacitated, and parents with twins are not invited for the study. Fathers/partners who are not living in the same municipality as the child are also not invited for the study.

### The study interventions

During the project’s first phase, the participants will receive the existing publicly available postnatal care services (CAU) in the 10 municipalities and these may vary as described in Table 2. In the project’s second phase, the participants will receive the UYB intervention integrated into the existing publicly available postnatal care services in the 10 municipalities. The dose of UYB will therefore vary according to the variation in the existing postnatal care services (Table 2).

**Table 2 Tab2:** Information on visits from the health visitor and ADBB observations in the 10 municipalities

	Number of visits from the health visitor 0–12 months postpartum	Infant's age (months) when ADBB is conducted	Number of ADBB observations in total	ADBB observation 2–3 months	ADBB observation 4–6 months	ADBB observation 8–10 months
*Municipality*						
Aalborg	5	2, 4–6, 8–10	3	X	X	X
Frederiksberg	5	4, 8	2		X	X
Holbæk	6	2, 4, 8	3	X	X	X
Hvidovre	7	2, 8–10	2	X		X
Høje-Taastrup	6	2–3, 4–6	3	X	X	
Køge	5	2–3, 4–6, 9–10	3	X	X	X
Lolland	7	2, 4, 6, 8	4	X	X	X
Middelfart	6	2, 4, 8	3	X	X	X
Nyborg	5	2, 8–10	2	X		X
Næstved	7	4	1		X	

ADBB = Alarm Distress Baby Scale

### Care As Usual

The Care As Usual (CAU) group of first time parents receives the existing publicly available postnatal care services in the 10 municipalities. The existing publicly available postnatal care services include home visits by health visitors throughout the infant’s first year. During the visits, health visitors measure and weigh the baby and guide and support the parents in a range of areas, such as breastfeeding, infant sleep, infant language, motor and physical development, and parental mental health. At some home visits, the health visitors also conduct an ADBB observation. The number of visits and the number of ADBB observations vary in the different municipalities but across municipalities, all first-time families are visited at least five times, and at least one ADBB observation is conducted during the infant’s first year. The five visits take place in the days following birth, when the infant is 2–4 weeks, 2–3 months, 4–6 months, and 8–10 months, while the ADBB observation is typically conducted at the 2–3 months and/or 4–6 months visit.

### The Understanding Your Baby intervention

In the study’s second phase, the experimental group of first time parents receives the UYB integrated into the existing publicly available postnatal care services, i.e. the amount of potential delivered UYB range from one to five in the 10 municipalities (see Table 2). The UYB is delivered by health visitors to all first-time parents during routine home visits.

The UYB is a universal educational parenting intervention aimed at supporting and promoting parents’ curiosity and knowledge about their infants’ socioemotional needs, ability to meet their infants’ needs, and thereby facilitating the development of a secure attachment and infant optimal socioemotional development. The UYB uses the routine ADBB observational situation as a standardized setting for a systematic sharing of knowledge and a dialogue with parents about their infants’ socioemotional cues, needs, and development in all families—i.e. this dialogue takes place in all cases—whether or not the ADBB observation gives rise to a concern regarding the infant’s socioemotional development. Although the primary purpose of the ADBB observation is early identification of persistent infant social withdrawal, the ADBB also provides an optimal context to guide caregivers about their child’s social and emotional development. During the interaction between the health visitor and the infant, the health visitor articulates specific infant behaviors and help the caregivers to interpret these behaviors in terms of mental states. For instance, when the infant looks away, the health visitor may explain to the parents that the infant needs a break to regulate themselves because interaction and eye contact is very stimulating for small children. In this way, the parents are shown their infant’s behavioral cues and how these behaviors are expressions of the inner world of the infant.

The UYB consists of four elements, each of which are described in the following: The UYB manual, the UYB dialogue cards, the UYB online video library, and UYB profiles on the social media platforms Facebook and Instagram.

The UYB manual entails an overview of research-based knowledge about infants’ socioemotional development and needs across four age groups (0–2, 2–4, 4–8, and 8–12 months) and five central behavioral areas inspired by the following items from the ADBB: Facial expressions (item 1), Eye contact (item 2), General level of activity (item 3), Vocalizations (item 5), Relationship and Attraction (items 7 and 8). In addition, the manual contains three chapters on significant themes for infant socioemotional development: infant crying, ‘good enough’ parenting, and screen time in the family. The manual provides the health visitors with the newest research-based knowledge on infant socioemotional development and enables them to provide research-based information to parents during the ADBB observations and when using the dialogue cards.

The UYB dialogue cards consist of four laminated cards, one that is mandatory and three that are optional for the health visitors to use. The mandatory UYB dialogue card is developed to support sharing of knowledge and facilitate reflection about the infant’s socioemotional cues and needs. The card displays the five areas from the ADBB also described in the manual. On the front of the card, short questions describe what the health visitor is observing when examining each of these areas, e.g. “What emotions does the baby express with his/her face?” (Facial Expressions). On the back of the card, short sentences describe how parents can support their infant’s development in relation to each of the areas, e.g. “Eye contact gives the baby a feeling of closeness and security. Breaks give the baby an opportunity to self-regulate. Notice when your baby seeks eye contact and when your baby needs a break.” This dialogue card should be used every time the health visitors conduct ADBB screenings in first-time families to inform parents about the specific areas related to infant social contact. Health visitors are also encouraged to use the card to provide feedback to parents about their infant’s behavior on each of these areas and guide parents in relation to how to support their child’s socioemotional development, also using age-specific and research-based knowledge from the manual.

The three optional UYB dialogue cards focus on infant crying, ‘good enough’ parenting, and screen time in the family. These cards may be used when health visitors believe that parents could benefit from talking about one of these topics. Each of these cards consists of a combination of research-based statements about the topic to increase parents’ knowledge, e.g. “Crying is the most important tool of the infant to express his/her needs and to achieve comfort and proximity form his/her parents”, and questions to facilitate reflection, e.g. “How is it for you when your infant is crying—what do you think and feel?”.

The UYB video library consists of videos categorized into the four age groups according to the manual, i.e. 0–2, 2–4, 4–8, and 8–12 months. The videos are designed to inform parents about their infant’s socioemotional needs and development, for example the development of the social smile (0–2 months), turn-taking (2–4 months), and social referencing (8–12 months). All videos contain clips of real parent-infant interactions exemplifying the socioemotional needs described by the speaker, e.g. an infant taking a break from the eye contact and the parent responding by reducing the amount of stimulation. Only examples of positive parenting behaviors are included in the videos. All videos are freely available online at the project homepage (www.forstaadinbaby.dk). It is a mandatory part of the UYB that health visitors inform first-time parents about the online video library (orally or via visiting cards). Health visitors are also encouraged to watch a video together with parents or groups of parents when possible.

Likewise, the health visitors may inform the parents about the UYB social media platforms. On the social media platforms, parents can find research-based knowledge about infant socioemotional development and parenting related to the first year of life. The same content is posted on Facebook and Instagram. Content are posted on the profiles regularly (typically twice a week), and both pictures and snippets of videos from the UYB video library are posted. The posted content is based on the research described in the UYB manual. In addition to posting research-based knowledge, the followers are engaged by Q&A’s (questions and answers) where they get an opportunity to ask questions about a specific topic, e.g. parent–child attachment, and then answers to selected questions are posted on the profiles the following weeks. The followers are also given a place to share their own experiences related to parenting by asking them questions and sharing their answers anonymously, e.g. “When are you most stressed as a parent?”. The aim is to communicate the research-based knowledge in a way that makes sense for all parents, and concrete examples of how the results can be translated into parenting behaviors are provided whenever possible. The concept of ‘good enough’ parenting is integrated into many of the posts to prevent or diminish some of the negative effects that new parenting information could create among the followers, e.g. that the parents feel that they should be doing all the things they read about on the profile all the time.

